### Participant timeline

Time schedule for enrolment, interventions, assessment and visits for participants is shown in table 2.

**Table 2 BMJOPEN2016012356TB2:** Schedule of trial procedures

	T0: As soon as possible after identification of a potential participant and to allow timely administration of trial treatment	T1: As soon as possible after enrolment*	T1+ 24 hours: 24 hours after first dose of trial treatment	T2: 24–36 hours after first dose of trial treatment	T2+ 24–48 hours: 24–48 hours after second dose of trial treatment	T2+7: 7 days after second dose of trial treatment	T3: On the day of discharge from acute care and up to 48 hours prior	T4: 4–6 weeks after discharge from acute care	T5: 6 months (±4 weeks) after randomisation	T6: 12 months (±4 weeks) after randomisation
Eligibility assessment	X									
Informed consent and assent (where appropriate)†	X						X‡		X‡	X‡
Enrolment	X									
Obtain relevant clinical data§	X	X	X	X	X	X	X	X	X	X
Randomisation	X	X ¶								
Scavenged samples§	X	X	X	X	X	X	X	X	X	X
Additional (research sample) where consent is given	X (baseline sample, prior to receipt of trial treatment: neuronal antibody testing, cytokine and DNA analysis, cellular immunology††)	X (where baseline sample not previously obtained and before administration of trial treatment)	X (functional genomics, DNA analysis**)			X (cellular immunology††, functional genomics, DNA analysis**)			X‡‡ (convalescent sample: neuronal antibody testing, cellular immunology†† and cytokine analysis, functional genomics)	
Mandatory full blood count check					X					
Administration of trial treatment and monitoring		X		X						
Completion of Data Capture Form and eCRF§	X	X	X	X	X	X	X	X	X	X
Adverse event assessment (AESIs, SARs, SUSARs and SAEs)		X	X	X	X	X	X	X	X	X§§
Questionnaire completion (ABAS-II, SDQ, GMFCS, Peds QL)								X	X	X
Liverpool Outcome Score								X		X
GOSE-Peds									X	X¶¶
Research MRI (where consent is given)									X***	
Neuropsychology assessment										X

*Visit must be 120 hours from presentation to any hospital OR, for transferred patients, 72 hours from admission to a recruiting hospital even if >120 hours has elapsed since presentation to the initial (referring) hospital.

†Participant consent if 16 years and assent if <16 years.

‡Where consent/assent (as appropriate) has not been previously obtained.

§Continuous process throughout the study.

¶First dose of trial treatment may be given on the same day as randomisation.

**Where DNA sample not previously obtained. Only one DNA sample is required.

††Selected centres only.

‡‡To avoid an extra visit solely for this purpose, the ‘6-month research sample’ can be obtained at any routine follow-up clinical appointments that occur after the participant has been discharged from acute care.

§§Only deaths or where a serious adverse event is judged to be directly related to the trial treatment.

¶¶Primary outcome measure.

***Where consent obtained. May not be required if having routine clinical MRI scan ≥3 months after randomisation.

### Trial duration

The trial is planned to last 5 years which includes a 42 months for recruitment, 12-month follow-up period for each participant and 6 months for data analysis.

### Sample size

There is a near paucity of RCT data from previous studies to estimate sample size for this trial. The sample size calculation is based on the assumption that detection of at least 20% difference from 43% in the ‘good recovery’ rate (ie, GOS-E-Peds score 2 or lower) by 12 months after randomisation is likely to be clinically significant. This is similar to a large observational study on autoimmune encephalitis.^18^ Based on this assumption, a total of 308 participants (154 per group), which takes into account an attrition rate of ∼10%, will provide 90% power and 5% level of significance for a two-sided test.

### Recruitment plan

A flow chart showing the process of patient recruitment is shown in figure 1. Eligible patients will be identified through various routes: by (1) clinicians reviewing medical handover lists and clinical records of new admissions; (2) research team contacting relevant hospital wards; (3) microbiologists and/or virologists identifying children who have had a lumbar puncture performed for suspected CNS infection; (4) radiologist identifying a brain MRI scan suggestive of encephalitis and (5) neurophysiologist identifying an EEG suggestive of encephalitis.

**Figure 1 BMJOPEN2016012356F1:**
[figure not shown]
Flow chart showing process of participant recruitment.

Following identification of a potential patient through any of the above routes, a member of the clinical team will approach the parent/guardian/legal representative to seek their interest in knowing more about the trial and verbal consent will be sought from the family for their details to be passed on to the trial team. Only if consent for this is granted will a member of the trial team contact the family. A member of the trial team will check the patient's eligibility with the parent/guardian/legal representative, after which they will be provided with the participant information sheet (PIS), if the patient is eligible, and given sufficient time to read this and make a decision regarding participation in the trial. The investigator must obtain informed consent and assent (where applicable and obtainable) before the patient undergoes any trial procedure(s). Once appropriate consent and assent (where applicable and obtainable) have been obtained, the patient will be enrolled to the trial by assigning them a participant number using the next available number from the prepopulated enrolment log.

To maximise achievability of the sample size, we have included mostly tertiary paediatric units that are well placed to recruit rapidly a high number of participants. Potential barriers to recruitment will be identified during the pilot phase of the trial, and close support will be provided to sites with recruitment difficulties. A robust system will be put in place to monitor recruitment to ensure that this is on target. A contingency plan will also be put in place to allow for opening of additional sites in the unlikely event of a less than expected recruitment. A ‘Screening log’ of all screened patients will be kept and will include patients with a diagnosis of encephalitis but are not eligible, eligible patients who refuse to be approached or may not be suitable to be approached, as well as those for whom consent was declined. The reason(s) why a patient is not enrolled will be clearly documented in the screening log, including reasons for declined consent, where this is provided.

### Randomisation

After eligibility is confirmed and consent (and assent where applicable) obtained, enrolled participants will be randomised as soon as possible to allow early administration of the trial treatment in line with the protocol. Randomisation will be performed using a fully validated online randomisation system developed by the Primary Care and Vaccines Collaborative Clinical Trials Unit, University of Oxford, and during working hours when the trial treatment are available. Participants will be randomised in a 1:1 ratio to either an intervention or control group. Only trained research staff with appropriate access and who are on the IgNiTE trial delegation log will be able to randomise patients. The incidence of encephalitis is higher in infants and some forms of encephalitis are more prevalent in certain age groups. In addition, as part of standard care, patients with inflammatory encephalopathy may receive steroid treatment, which may have a beneficial effect. Therefore, to ensure balance between the trial groups, and account for steroid use as confounding variable, randomisation will be stratified by age group n=5 (<1, 1–4, 5–9, 10–14 and 15+ years), and steroid use (yes/no) at the time of enrolment, and using randomly varying block sizes. A computer-generated randomisation code at the time of randomisation will ensure concealment of allocation.

### Withdrawal from trial treatment

The participant will be discontinued from the trial treatment at any time if the investigator considers it necessary for any reason including:
ineligibility (either arising during the trial or retrospectively having been overlooked at screening),significant protocol deviation,significant non-compliance with treatment regimen or trial requirements,an adverse event (AE) which requires discontinuation of the trial treatment or results in inability to continue to comply with trial procedures,disease progression which requires discontinuation of the trial treatment or results in inability to continue to comply with trial procedures.

A participant may also voluntarily withdraw from the trial treatment due to what he or she perceives as an intolerable AE, or for other reasons if they wish.

### Blinding

IgNiTE is a double-blind trial and a rigid blinding process will be in place throughout the trial to ensure validity of the data collected. Participants and their parents/guardians/legal representatives as well as all research staff involved in any aspect of the trial conduct, including recruitment, administration of trial treatment, carrying out trial assessments, data collection and entry, sample and statistical analyses, will be blinded to treatment allocation throughout the entire trial period. There will be separate monitors for blinded and non-blinded data. The active treatment and placebo will be visually identical (packaged and labelled in the same manner) and administered at the same dose and infusion rate to maintain blinding. To be able to manage trial treatment stock effectively and minimise wastage, the clinical trials pharmacists at each recruiting site who are independent of the trial will be non-blinded. The tear off section of the label will inform the dispensing pharmacist of the true nature of the contents (IVIG or placebo). At dispending, this section of the label will be removed to maintain blinding.

Unblinding of treatment allocation will occur only in exceptional circumstances when knowledge of the actual treatment received is absolutely essential for further management of the participant. Unblinding will be performed via the online randomisation system. The decision to unblind a participant's treatment allocation will be solely that of the site investigator. Only individuals given access to unblind will be able to do this and will include the site pharmacist, principal investigator and coinvestigators. Where there is a problem with Sortition, unblinding will be available via either the site pharmacist (during work hours) or a non-blinded staff member in Oxford (out of hours) who is independent of the trial, both of whom will have secure access to the master randomisation list for this purpose.

### Data collection methods

Trial data will be collected by delegated research staff with appropriate training using two methods: (1) a paper-data capture form and (2) an electronic case report form (CRF), OpenClinica which is a password-protected, web-based database with accountability records that is stored on a secure sever within the UK. Trial data will be obtained from various sources, including patient medical notes, parent interview, laboratory reports, brain scan pictures and reports, EEG reports, pharmacy records, drug charts, questionnaires and any correspondences relating to the participants involvement in the trial.

Different data types will be collected throughout the trial period.

#### Clinical data

These will include information regarding patient demographics, clinical findings, treatment, investigation results, length of hospital stay and intensive care management. These data will be obtained throughout the participant's time in the trial (table 1).

#### Questionnaires and outcome measures

Validated questionnaires assessing behaviour, motor and adaptive functioning and quality of life will be completed by the participant and/or by their parent/guardian/authorised legal representative at: (1) 4–6 weeks following discharge from acute care and (2) 12 months after randomisation:
Adaptive Behavior Assessment System, second edition,^23^
^24^Gross Motor Function Classification System,^25^Strength and Difficulties Questionnaire,^26^Paediatric Quality of Life Inventory.^27^
^28^

Outcome scores will be assessed using the (1) Paediatric version of the Glasgow Outcome Score Extended (GOSE Peds) at 6 and 12 months after randomisation and (2) Liverpool Outcome Score (LOS) at 4–6 weeks after discharge from acute care and 12 months after randomisation.

Various measures to obtain complete follow-up data will be implemented: (1) blinded research staff or the participant's clinician can assist with questionnaires, (2) prepaid envelopes will be provided for return of questionnaires and families will be reminded by telephone, post and/or email and (3) the primary outcome (GOSE Peds) assessment will be completed by the neuropsychologist at the 12-month visit. The neuropsychologist may also assist with questionnaire completion.

#### Laboratory data

Blood and CSF samples (only obtained at the same time as routine lumbar puncture) will be obtained from participants at different time points for neuronal antibodies, cytokine, functional genomics, DNA and cellular immunology evaluation are optional (table 2). A mandatory blood sample will be obtained at 24–48 hours following the second dose of trial treatment to assess full blood count levels as a risk mitigation measure to monitor for haemolysis, which is a reported side effect of high-dose IVIG treatment. Blood sample volumes will be in line with the Medicines for Children Research Network recommendation.^29^ CSF volumes will be in line with British Infection Society TB guideline.^30^ All samples will be anonymised. A sample collection and processing guide will be made available to all recruiting sites.

#### Radiological data

All brain scans (and reports) performed as part of routine clinical care during the study period will be collected. An optional research MRI scan will be performed around 6 months after randomisation for participants who consent to this and where a routine follow-up clinical scan is not being performed. Where a clinical scan is planned for ≥3 months after randomisation, this will be used instead and a research MRI scan will not be necessary. All scans will be anonymised and sent to Great Ormond Street Hospital, London, for analyses by a blinded study neuroradiologist and imaging scientist. MRI findings will be correlated with the primary neurological outcome assessed at 12 months postrandomisation. Further exploratory correlations with other neurological outcomes assessed at the different study time points will also be performed.

#### Neuropsychology assessment

This will be performed at 12 months after randomisation by a blinded trial neuropsychologist using age appropriate, validated scales of developmental assessment (see table 1).

#### Adverse events

Information on AEs will be collected throughout the trial (see the Harms section).

### Withdrawal

Participants may withdraw from the trial at any time. No further data will be collected. Data collected up until the point of withdrawal from the trial will be analysed unless the parent/participant decides against this. If a participant is withdrawn due to an AE, the investigator will follow this up until it resolves or stabilises. All participants who are withdrawn from trial treatment (see the Withdrawal from trial treatment section) will remain in the trial and followed up as per the trial protocol, but will not have any invasive procedures performed. The trial data will be analysed on an intention-to-treat (ITT) basis; therefore, all withdrawals, either from the trial or from the trial treatment, will be reported and included in the data analyses. All protocol deviations will also be reported.

### Study data

#### Data management

Data management will be via the OpenClinica database. All relevant data recorded elsewhere (see data collection methods) that are required to achieve the trial objectives will be transferred on to the OpenClinica database from where they can be downloaded for analysis. To maintain a high-quality standard of data entry, the database will be tested and validated prior to use. In addition, research staff will receive appropriate level training on data collection and entry and there will be regular monitoring of trial data throughout the trial. Furthermore, prior to data analysis, the database will be locked for cleaning to ensure that data are complete and reliable. Research staff at the various recruiting sites will be contacted to provide information on any missing data and to clarify any errors identified. All trial documents will be retained and stored securely in accordance with GCP after the completion or discontinuation of the trial for 3 years after the youngest participant turns 18 years.

### Statistical methods

The primary statistical analysis will be carried out on the basis of ITT. After randomisation, participants will be analysed according to their allocated treatment group irrespective of what treatment they actually receive. However, a further modified ITT analysis will be performed excluding participants found to be ineligible in retrospect.

Data analysis will be performed using a mixed effect model for repeated measures, that is, to incorporate all outcome data collected during the 12 months follow-up, in order to apply the ITT principle as far as possible and to account for potential biases arising from loss to follow-up. The model will include treatment group, time, treatment-by-time interaction and baseline covariates. An unstructured correlation matrix will be used to model the within-participant error correlation structure. An appropriate contrast will be specified to test for treatment efficacy between randomised groups at 12 months. Various sensitivity analyses will be performed using other imputation methods, as well as analysis of 12-month data cross-sectionally, to test whether the results are robust to different assumptions about the missing data. The primary ITT analysis will account for steroid use before randomisation as a covariate. As required, the impact of posthospitalisation course including the use of concomitant and/or different immune treatments and period of neurorehabilitation on the primary outcome will be investigated in an exploratory analysis.

The results from the trial will be prepared as comparative summary statistics (difference in response rate or means) with 95% CIs. All the tests will be performed at a 5% two-sided significance level. A full detailed analysis plan (including plans for any interim analysis, subgroup analysis and sensitivity analysis) will be prepared and finalised before the first interim analysis.

#### Primary analysis

The primary efficacy end point in this trial is ‘good recovery’, defined by GOS-E-Peds score 2 or lower, at 12 months from randomisation. This will be analysed using a generalised linear mixed effect model, using data collected at discharge, 6 and 12 months from randomisation. An interaction between time and randomised group will be fitted to allow estimation of treatment effect at each time point. The model will adjust for baseline values and other stratification factors (eg, age and steroid treatment at the time of randomisation).

#### Secondary and tertiary analyses

As far as possible, we will use similar method for secondary and tertiary continuous outcomes collected at multiple time points or analysis of covariance for those collected at 12 months only, adjusting for baseline measures (if collected) and any stratification variables. Otherwise, an equivalent non-parametric method will be used for outcomes that violate the normal distribution assumption. A log-binomial regression will be performed on binary outcomes with similar adjustment of baseline covariates. χ^2^ or Fisher's exact test will be used to analyse AEs and non-adherence.

Reporting of the trial findings will be in line with Consolidated Standards of Reporting Trials (CONSORT) guidelines.

### Interim analysis

Analysis for the DSMC will be performed in accordance with the DSMC Charter. No interim efficacy analysis will be performed. Interim reports containing safety data, along with any other analyses that the committee may request, will be sent to the DSMC in strict confidence. Close monitoring to assess practical aspects of delivering the trial interventions and recruitment will also be undertaken.

### Data monitoring

The Data Safety Monitoring Committee (DSMC) is responsible for safeguarding the interests of trial patients, monitoring the accumulating data and making recommendations to the Trial Steering Committee (TSC) on whether the trial should continue as planned. The DSMC will comprise of a clinical chair, clinicians and a statistician, all of whom will be independent of the trial, the sponsor and funders. The role of the TSC is to provide overall supervision for the IgNiTE trial on behalf of the Trial Sponsor and the Trial Funder and to ensure that the IgNiTE trial is conducted according to the guidelines for GCP, Research Governance Framework for Health and Social Care and all relevant regulations and local policies. The TSC will comprise an independent chair, the chief investigator (CI), paediatricians and patient representatives. In discharging its safety role, the TSC will work in conjunction with DSMC for the IgNiTE trial. DSMC and TSC will meet prior to trial start and 6 months thereafter. Increased frequency of meetings will be arranged depending on the requirements of the trial, DSMC and TSC recommendations.

### Stopping guidelines

This trial may be suspended or prematurely terminated by the sponsor, CI, regulatory authority or funder if there is sufficient reason to think that the safety of participants is affected by the trial procedures. Written notification, documenting the reason for trial suspension or termination, will be provided by the suspending or terminating party to the investigator, funders and regulatory authorities. If the trial is prematurely terminated or suspended, the CI will promptly inform the REC, MHRA and CSL Behring and will provide the reason(s) for the termination or suspension.

### Harms

International Conference on Harmonisation (ICH) definitions are used for AEs, adverse events of special interest (AESIs), adverse reactions (ARs), serious AEs (SAEs), serious adverse reactions (SARs) and suspected unexpected SARs (SUSARs). IVIG has a well-established side-effect profile. All participants will be monitored for (1) AESIs (includes anaphylaxis, haemolysis, new-onset seizure or abnormal movements not thought to be due to the encephalitis illness, thromboembolism, aseptic meningitis unrelated to the encephalitis illness, acute renal failure and any other medically significant events as determined by the investigator), in the first 5 days following receipt of trial treatment, (2) SAEs up to 6 months after randomisation, or up to 12 months after randomisation where the event is judged directly related to the trial treatment and (3) deaths up to 12 months after randomisation.

Monitoring and reporting of AEs will be performed by the site PI and research team, and will be recorded on the data capture form and uploaded to the eCRF (OpenClinica). The nature and severity of each AE, and the relationship to trial treatment will be documented. The expectedness of an AE will be determined by whether or not it is listed in the SmPC for Privigen or Human Albumin Solution. AESIs and SAEs will be reported to the CI and CSL Behring within 24 hours of the research staff becoming aware. The CI will notify the DSMC of all AESIs and SAEs. This will be expedited (within 24 hours of the CI becoming aware), for all AESIs and for all SAEs that are judged related to the trial treatment. Those that are judged to be unrelated to the trial treatment do not require expedited reporting to the DSMC.

The CI will report all relevant information about a suspected unexpected adverse reaction (SUSAR) that occurs during the course of the trial to the MHRA, CSL Behring, the relevant ethics committee and the DSMC. For fatal and life-threatening SUSARS, this will be performed no later than 7 calendar days after the Sponsor or delegate is first aware of the reaction. Any additional relevant information will be reported within 8 calendar days of the initial report. All other SUSARs will be reported within 15 calendar days. The CI or delegate will also inform all principal investigators concerned of relevant information about SARs that could adversely affect the safety of participants.

A summary list of all SAEs (including those unrelated to the trial treatment), AESIs and SUSARs will be provided in a safety report to the DSMC, which will be submitted at regular interval as specified in the DSMC Charter. In addition, a strict data sheet will be kept which will include the randomisation code aligned to the batch number of assigned IVIG product and in order to maintain a link between the participant and the batch of the product.

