### Secondary objectives

The secondary objectives are
to compare (1) clinical and (2) further neurological outcomes of children with encephalitis who have been treated with IVIG or placebo, in addition to standard therapy,to confirm the safety of IVIG treatment for children with encephalitis,to identify the proportion of children with immune-mediated encephalitis,to determine the effect of IVIG treatment on neuronal antibody levels in children with immune-mediated encephalitis.

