### Eligibility criteria

*Inclusion criteria (based on the International Encephalitis Consortium consensus case definition)*^1^
Age 6 weeks to 16 years old,Acute (within 24 hours) or subacute (24 hours to 4 weeks) onset of altered mental state (reduced or altered conscious level, irritability, altered personality or behaviour, lethargy) not attributable to a metabolic cause,At least two of:
fever >38°C within 72 hours before or after presentation to hospital,new or acute onset brain imaging consistent with encephalitis or immune-mediated encephalopathy,CSF white cell count (WCC) >4/microlitre,generalised or partial seizures not fully attributable to a pre-existing seizure disorder,new-onset focal neurological signs (including movement disorders) for >6 hours,EEG abnormality that is consistent with encephalitis and not clearly attributable to another causeandParent/guardian/legal representative consent to the patient participating in the trial.

Exclusion criteria

The patient will not be enrolled to the trial if any of the following apply, in addition to failure to meet all the inclusion criteria:

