#### Secondary and tertiary outcomes

These are outlined in table 1.

**Table 1 BMJOPEN2016012356TB1:** Secondary and tertiary outcomes

Data collection time point	Outcome measure
*Secondary outcomes*	
Clinical and neurological	
During hospital inpatient stay	Glasgow coma score Neurological examination findings as documented by the clinical team Duration of invasive ventilation (if ventilated) Length of intensive care unit (ICU) stay in a subset of children admitted to ICU Length of hospitalisation
Around 4–6 weeks after discharge from acute care	Strength and Difficulties Questionnaire (SDQ) Adaptive Behavior Assessment System-Second Edition (ABAS-II) Peds Quality of Life scoring algorithm Liverpool Outcome Score Gross Motor Function Classification System (GMFCS)
Around 6 months (±4 weeks) after randomisation	GOSE-Peds
Around 12 months (±4 weeks) after randomisation	New diagnosis of epilepsy Use of antiepileptic treatment Strength and Difficulties Questionnaire (SDQ) Adaptive Behavior Assessment System-Second Edition (ABAS-II) Peds Quality of Life (PedsQoL) scoring algorithm Liverpool Outcome Score (LOS) Gross Motor Function Classification System (GMFCS) Blinded neuropsychologist assessment of cognitive functioning using age appropriate developmental scales (Bayley Scales for Infant Development (BSID-III)/Wechsler preschool and Primary Scale of Intelligence III (WPPSI-III)/Wechsler Intelligence Scale for Children IV (WISC-IV)
12 months after randomisation	Proportion of deaths occurring in participants
Radiological	
Around 6 months after randomisation	Brain MRI to assess lesion resolution, presence of new lesions and distribution of persisting disease
Safety	
24–48 hours after the second IMP dose	Full blood count check to monitor for haemolysis
First 5 days after each dose of trial treatment	Adverse events of special interest (AESIs)
Up to 6 months after randomisation	Serious adverse events (SAEs)
Up to 12 months after randomisation	Serious adverse reactions (SARs)Suspected Unexpected Serious Adverse Reactions (SUSARs)
Autoimmune	Presence of and comparison of levels of specific neuronal antibodies in serum and/or CSF samples (where lumbar puncture is performed as part of routine care) before and after administration of trial treatment

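### Seizures, abnormal movements and aseptic meningitis are events of special interest only if judged not due to encephalitis, so a non-serious excess on IVIG may be under-detected

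*Protocol article*

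**What the plan says.** One of the secondary objectives is "to confirm the safety of IVIG treatment for children with encephalitis". The Harms section gives three monitored groups: AESIs, SAEs and deaths. Within the AESI list, anaphylaxis, haemolysis, thromboembolism and acute renal failure count without condition. Seizures, abnormal movements and aseptic meningitis count only with a causal judgement: "new-onset seizure or abnormal movements not thought to be due to the encephalitis illness, thromboembolism, aseptic meningitis unrelated to the encephalitis illness". The list ends with a catch-all, "any other medically significant events as determined by the investigator". Table 1 sets the AESI window as "First 5 days after each dose of trial treatment".

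The eligibility criteria require at least two of six features. These include "generalised or partial seizures not fully attributable to a pre-existing seizure disorder", "CSF white cell count (WCC) >4/microlitre", fever, and new focal neurological signs, among which movement disorders are named.

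The analysis section states that "χ^2^ or Fisher's exact test will be used to analyse AEs and non-adherence". The short Adverse events paragraph under data collection says that AEs are collected throughout and refers the reader to Harms. Table 1's safety outcomes are a full blood count, AESIs, SAEs, SARs and SUSARs. The adverse event row of Table 2 names the same four event categories.

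**The concern.** The causal condition falls on the events that look like the disease, at the time when the disease is active. Treatment starts within days of presentation and the AESI window is the following few days. A site seeing a seizure in a child with acute encephalitis may reasonably put it down to the illness. If the drug caused it, it then leaves the AESI count.

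In a blinded randomised trial, causation can be assessed for the group by comparing event rates between arms, without deciding it for each child. A definition that filters on individual causation before the comparison gives up part of that advantage. What is at stake is the safety objective: a real but non-serious excess of these events could be diluted in the AESI table. If the filtered-out events were never recorded, they could not be recovered at analysis.

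**Working it through.** **Where would a non-serious event judged due to encephalitis be held?**

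| Place in the protocol article | Is it covered? |
|---|---|
| AESI list (Harms) | No, excluded by the causal condition |
| AESI catch-all (Harms) | Only at the investigator's discretion |
| SAEs to 6 months (Harms) | No, because it is not serious |
| SARs and SUSARs (Tables 1 and 2) | No, because it is neither serious nor judged drug-related |
| General statements on AEs (data collection, Harms, analysis) | Unclear: no category or window is given beyond those above |

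A serious event is an SAE whatever its presumed cause, and unrelated SAEs are included in the summary list for the DSMC. The gap is therefore confined to non-serious events.

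**How much could be lost?** The article gives no seizure rate and no misattribution share, so there is no figure on this point to reproduce. The only documented input is 154 per group (Sample size section). That figure is consistent with its stated basis: 43% against 63%, 90% power, two-sided 5%, with continuity correction, gives 139 per arm, and 139/0.90 = 154.4.

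Assumptions, for illustration only:
- True rates of new seizure in the window: 25% on placebo, 40% on IVIG, so a 15-point drug-caused excess.
- 90% of background seizures are attributed to the illness in both arms, because attribution is blinded.
- A share s of the drug-caused seizures is also attributed to the illness.

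The AESI rates are then 0.25 × 0.10 = 0.025 on placebo and 0.025 + 0.15 × (1 − s) on IVIG.

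Power, with n per arm, d the difference and p̄ the mean of the two rates, is Φ[(d − 1.96·√(2p̄(1−p̄)/n)) / √((p₁(1−p₁)+p₂(1−p₂))/n)].

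All seizures, 25% against 40%: d = 0.15 and p̄ = 0.325. The null standard error is 0.0534 and the alternative 0.0527. (0.15 − 0.1046)/0.0527 = 0.86, so power is 0.81.

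AESI count at s = 0.50, 2.5% against 10%: d = 0.075 and p̄ = 0.0625. The standard errors are 0.0276 and 0.0273. (0.075 − 0.0541)/0.0273 = 0.77, so power is 0.78.

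| Drug-caused events misattributed (s) | AESI rates, placebo vs IVIG | Power of AESI count | Power of all-event count |
|---|---|---|---|
| 0% | 2.5% vs 17.5% | 0.99 | 0.81 |
| 25% | 2.5% vs 13.75% | 0.95 | 0.81 |
| 50% | 2.5% vs 10% | 0.78 | 0.81 |
| 75% | 2.5% vs 6.25% | 0.36 | 0.81 |
| 90% | 2.5% vs 4% | 0.11 | 0.81 |

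**Other rates.** With a 20% background and a 10-point excess, the AESI count has power 0.93, 0.81, 0.56, 0.23 and 0.08 at the same five shares, against 0.53 for all events. With a 10% background it runs from 0.96 down to 0.11, against 0.69. With a 30% background it runs from 0.90 down to 0.07, against 0.45. In all four settings the two counts have about equal power when roughly half of the drug-caused events are misattributed. That crossing point depends on the assumed 90% for background events.

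**The case against.** The strongest reply is that the article does provide for adverse events in general. It says that AEs are collected throughout, that the nature, severity and relationship to treatment of each AE are documented, and that AEs are compared between arms by χ² or Fisher's exact test. On that reading a seizure attributed to the illness is still recorded and compared. This has some force: the text is ambiguous rather than plainly exclusionary, and the full protocol may settle it. But the data collection sentence refers back to Harms, Harms opens with a closed list of three monitored groups, and Tables 1 and 2 repeat specific categories with no place for this event. The general sentences do not reliably secure it.

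The second reply is that filtering can help. It removes background events and so raises power when attribution is accurate. That stands, as the table shows, and it is a reason to keep the attributed count.

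Third, inpatient neurological findings, new epilepsy and antiepileptic use are outcomes without any causal condition. That is also true. Of these, epilepsy and antiepileptic use are assessed at 12 months and do not measure tolerability in the days after dosing.

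Stronger readings are tempting but not supported:
- A reader might infer that harm from treatment will vanish from the arm comparison. Serious events do not, and for the others misattribution is a risk, not a certainty.
- A reader might infer bias between arms. Those who attribute events are blinded.
- A reader might infer that nearly every child enters with one of these features. Any two of six suffice, so fever with imaging or EEG findings qualifies without seizure, movement disorder or CSF white cells.
- Aseptic meningitis is not itself an entry criterion. The overlap is indirect.

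**Conclusion.** The point holds as a limited weakness in safety capture. The AESI count for seizures, abnormal movements and aseptic meningitis depends on individual attribution in a setting where drug effect and illness can look alike, and the non-serious events filtered out have no clearly stated home. The AESI comparison may therefore under-detect a non-serious excess. The loss is one of sensitivity.

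Its size cannot be fixed from the document. Under the assumed 25% against 40%, with 90% of background events attributed to illness, AESI power ranges from 0.99 to 0.11 as misattribution of drug-caused events goes from none to 90%, against 0.81 for all events. The filtered count is the better one below roughly half misattributed and the worse one above. It would be wrong to conclude that the definition always costs power. The sound conclusion is that the trial cannot know which case it is in if it holds only the filtered count.

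**What to change.** Keep the present attributed definition for expedited reporting. For the safety outcome in Table 1, record every new or worsening seizure, every abnormal movement and every diagnosed aseptic meningitis in the 5 days after each dose, regardless of presumed cause, with the investigator's attribution as a separate field. Compare these events by arm alongside the attributed count, and include both in the DSMC report. State in Harms and in Table 2 that these non-serious events are recorded.

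The cost is one or two eCRF fields in the dosing window, where clinical data are already captured continuously, and one safety table. No expedited reports are added. The downside is that background illness events add noise to the unfiltered table, which is why it should stand beside the attributed count and not replace it.
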